**Abbreviations**

| **CRF** | Case Report form |  |
| --- | --- | --- |
| **GCP** | Good clinical practice |  |
| **ICH** | International conference on harmonization of technical requirements for registration of pharmaceuticals for human use |  |
| **ISF** | Investigator site file |  |
| **ITT** | Intention to treat |  |
| **SAP** | Statistical Analyze Plan |  |
| **TMF** | Trial master file |  |
| **ETT** | Endotracheal tube |  |
| **VL** | Videolaryngoscopy |  |
| **C & L** | Cormack and Lehane | |
| **POGO** | Percentage of glottic opening | |
| **VAS** | Visual Analog scale | |
| **CO_2_** | Carbon Dioxide | |
| **OSAS** | Obstructive Sleep apnea Syndrome | |
| **SOP** | Standard Operating Procedure | |
| **CCD** | Charged Coupled Device | |
| **CMOS** | Complementary Metal Oxide Semi-conductor | |
| **RCA** | Radio Corporation of America | |
| **LED** | light emitting diode | |

**Study Protocol Overview**

| **Title** | Using King Vision video laryngoscope with a channeled blade prolongs time for tracheal intubation |
| --- | --- |
| **Short Title** | King Vision-Study |
| **Principal Investigator** | [name] |
| **Study Protocol-Code** | 1.1 |
| **Indication** | Patients having elective surgery with general anaesthesia and requiring mechanical ventilation via an endotracheal tube are recruited |
| **Primary Endpoint** | Comparison of the overall intubation time between the Channeled and the Standard Blade |
| **Secondary Endpoints** | Time Sequences:  1. Time to View of the Glottic  2. Time to Place the ETT  3. Time to Ventilation  4. View (C&L, POGO)  5. Five Point Likert Scale: 1 very easy –  5 very difficult |
| **Study design** | Prospective, controlled, monocenter, randomized |
| **Patient Selection** | Inclusion criteria:   - Age ≥ 18 Years - Elective surgery   Exclusion criteria:   - Pregnancy - ASA Class IV - Participation in other Studies - Unable to provide informed written consent - Risk for aspiration - Above one predictor for an anticipated difficult airway |
| **Duration of study** | The first patient expected in May, 2015. Completion of the last patient at November 2015. Duration of the study: 6 months. |
| **Number of patients** | 44 (22 Patients for each group) |
| **Statistics** | The respective times until first ventilation analyzed with the Wilcoxon test. Time to view/ -placed the ETT tested using the t-test. For all statistical tests, p values of 0.05 or less will be taken to indicate a significant difference. |

| **Accountability**   \| **Principal Investigator** \| Name [name]  Adress [name]  Phone [name]  Fax [name]  E-Mail [[contact]](mailto:[contact]) \| \| --- \| --- \| \| **Study Nurse** \| Name [name]  Adress [name]  Phone [name]  Fax [name]  E-Mail [[contact]](mailto:[contact]) \| \| **Statistic** \| Name [name]  Adress [name]  [contact]  Fax [name]  E-Mail [[contact]](mailto:[contact]) \| |
| --- | --- | --- | --- | --- | --- | --- |

**1. Introduction**

**1.1 Background**

The King Vision® VL (King Systems Corporation, Noblesville, IN 46060, USA; German sales by Ambu® GmbH, Bad Nauheim, Germany) is used in preclinical and in-hospital airway management since its market introduction 2013. The tracheal intubation using a direct laryngoscope requires a alignement of the oropharyngeal axis and the technique is difficult to learn (1,2). The King Vision® Vl consists of a 2.4-inch reusable Display on the handle with battery compartment for three AAA batteries (1.5 V) to the power line and the end of the stylet with a OLED (Organic Light Emitting Diode). At the lower end of the stylet is a CMOS chip and an LED light source. By CMOS chip technology, an automatic white balance and automatic focusing is performed (3). Using anti-fogging solution before use of the instrument omitted. The image transfer can be projected through an RCA connector (standard video input) to an external monitor. The channeled blade should facilitate to place the ETT, therefor no stylet is required. With the non-channeled blade, the intubation is facilitated by using a flexible stylet (4). In one manikin study, the King Vision® channeled blade compared with the standard blade (4). The learning curve using the King Vision VL is rapid, six applications using the standard blade and 4 applications with the channeled blade (4).

**1.2 Rationale for the clinical study**

So far the King Vision® standard blade compared with the channeled blade is only evaluated in manikin studies. Clinical trials with anesthized patients are missing in the database. The channeled blade brings likely through its preloading of the ETT in the guided channel and the positioning in front of the glottis, a possible time advantage. When using the standard blade, the ETT with a stylet can only placed after visualization of the glottis. This procedure is standardized in handling with the video laryngoscopy without tube guiding channels.

The primary endpoint in this proposed study is the time to ventilation, as measured by the apparent end-tidal CO_2_ wave on the anesthesia ventilator, of the standard and the channeled blade.

The Establishment of VL with different Blade systems and camera chip technology has improved in recent years, thanks to technical improvements and rigorous clinical observation, the airway management in anesthesia and intensive care. Thanks to this innovative technology, situations in which no positioning of the endotracheal tube are possible, become less frequent. The comparative analysis of these two studies blades are used for an optimization of the patient safety (shorter intubation time, minimizing damage to teeth / soft tissue). Secondly, the test results generated under standardized conditions should provide an impetus to other hospitals with regard to economic aspects that may contribute to the purchase of the two devices. Currently, only 4 - 7% of all German hospitals using Videolaryngoscope in their daily clinical routine (Stand at moment).

**1.3 Risk- benefit ratio**

Both devices are used according to their authorization of the manufacturer and study personnel are familiar with their use in the daily routine. The anesthesia implementing performed according to the SOP of the Department of Anesthesiology and there are no specific risks above the normal anesthesia routine. Furthermore, the time for anesthesia not prolonged through the study-related activities. There are no changes in this clinical trial neither the treatment or medication of the patients.

The incidence of teeth injury is frequently lower in contrast to the conventional laryngoscopy (5,6).

The principal investigator will be informed about all the details of relevant and new results, including adverse events related to study treatment.

**2. Objectives**

The aim of this study is to compare the King Vision® standard blade with the channeled blade with respect to their time to first ventilation, view of the glottic and evaluation about the handling.

**2.1 Primary Endpoint**

The primary endpoint of the study involves the comparison of the two blades in terms of time to the first ventilation (shown after three breaths through an end-tidal CO_2_ - wave on the anesthesia ventilator). The time limit for the intubation attempt amounts to 120 seconds.

**2.2 Secondary Endpoints**

Comparing the respective times of both devices for:

1. Time to View of the glottis (defined by removing the mask for

preoxygenation to the individual view of the glottis)

2. Time to Place of the ETT into the trachea (defined as the time from the point

of view of the glottis until disappearance of the black marker of the ETT

behind the glottis)

3. Time to Ventilation (shown after three breaths through an end-tidal CO_2_ -

wave on the anesthesia ventilator

3. Visualization of the laryngeal structures (C & L grade and POGO scale score)

4. Assessment of both blades by the user (using the 5 point Likert Scale: 1 very

easy - 5 very difficult)

**3. Study Design**

This is a prospective, single-center, randomized, controlled study. The randomization of study participants carried out centrally by the Study site of Department of Anesthesiology, University Medical Mainz, Germany by a 1:1 Randomization (QuickCalcs GraphPad, La Jolla, CA, USA).

**3.1 Timeline**

The Clinical Trial will begin after receipt the positive votum of the ethic committee. At this moment the clinical trial will likely during 6 Months (May - November 2015). Both the current total length of the study as well the period of recruitment of the patients can vary.

**3.2 Number of Patients**

44 participants (22 patients for each group) are planned to include in the clinical trial. Each Patient will be included only one in the study.

**3.3 Eligibility criteria**

**Inclusion criteria**

Patients in which all of the following criteria are met, can be included in the clinical study:

- Age ≥ 18 Years
- elective surgery

**Exlcusion criteria**

- Pregnancy
- ASA Class IV
- Participation in other Studies
- Unable to provide informed written consent
- Risk for aspiration
- Above one predictor for an anticipated difficult airway

**3.5 Early termination of the study**

For the following reasons , the entire clinical trial might be canceled at the discretion of the principal investigator :

- Occurrence of unknown, adverse events or events with considerable frequency and severity
- Medical or ethical reasons, the adverse effect on the further implementation of the clinical trial
- Inadequate recruitment of study participants
- For each study participant / patient participation in the study will be canceled under the following circumstances :
- Unexpected emergency or situation under a Difficult Airway

Management

- Verbal withdrawal of consent for study participation by the patient
- Patients who discontinue study participation prematurely replaced

The ethics committee must be informed.

**4. Interventions**

**Concomitant treatments in both groups**

Before the start of patient recruitment, the study personal accesses the eligibility criterias and the patients are evaluated for factors known to predict diffult intubation (e.g BMI, mouth opening, thyromental distance, Mallampati score). The results of this evaluation are recorded in a CRF sheet. Afterwards its necessary to get a written informed consent of the patient.

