**5. Statistic**

**5.1 Sample Size**

On the basis of previous data (4,7) we expected a difference of five seconds in time to ventilation in the channeled blade group. Assuming that using channeled blade abbreviated the time to ventilation with a Power of 90 %, 22 patients are needed in each group, that is, 44 patients at all.

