**5.2 Analysis of the primary outcome**

All data were exported from our CRF into MS Excel (Microsoft, Redmond, WA, USA) for analysis. Statistical testing was performed using Prism 7 (Graph Pad Software, La Jolla, CA, USA). The time to ventilation will be compared between the two groups using the Wicoxon-Mann-Whitney-test. A p-value of <0.05 was considered significant.

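### Airway-difficulty predictors are recorded at baseline, but the primary test ignores them; adjusting for one or two would be a cheap gain in precision

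*Protocol*

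**What the plan says.** Section 4 (Concomitant treatments in both groups) has study staff evaluate patients, before consent and surgery, for "factors known to predict diffult intubation (e.g BMI, mouth opening, thyromental distance, Mallampati score". It adds: "The results of this evaluation are recorded in a CRF sheet".

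The only stated use of these values is eligibility. Section 3.3 excludes patients with "Above one predictor for an anticipated difficult airway", so patients with no predictor and patients with one are both enrolled.

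Allocation is described in section 3 as "by a 1:1 Randomization (QuickCalcs GraphPad, La Jolla, CA, USA"; no stratification factor is named.

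Section 5.2 fixes the primary analysis: "The time to ventilation will be compared between the two groups using the Wicoxon-Mann-Whitney-test". No covariate enters it. The significance threshold is given as "A p-value of <0.05 was considered significant".

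Section 5.1 plans on this basis: "we expected a difference of five seconds in time to ventilation in the channeled blade group", and "with a Power of 90 %, 22 patients are needed in each group, that is, 44 patients at all". It states no SD.

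**The concern.** The protocol itself identifies these baseline values as predictors of difficult intubation. If they also explain part of the variation in time to ventilation, a test that ignores them leaves that variation in the error term. With 22 patients per arm and no stratification, one arm can also receive somewhat harder airways by chance, and nothing in allocation or analysis allows for that.

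At stake are some power and the accuracy of the one estimate the trial will produce. A rank-based primary test is no obstacle, because rank ANCOVA (Quade's test) is its covariate-adjusted counterpart.

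**Working it through.** **Inputs.** From the protocol: difference 5 s, 22 per arm, 90% power, threshold 0.05 (sections 5.1 and 5.2). Assumed: two-sided testing, normally distributed times, the SD, and the correlation ρ between a predictor and time to ventilation (R² = ρ²).

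**The plan's own figure.** Without an SD, 22 per arm cannot be derived from the protocol. With SD 5 s, the normal formula gives n = 2 × (1.960 + 1.282)² × (5/5)² = 21.02, rounded up to 22. A two-sided t-test with 22 per arm reaches 90% at SD 5.00 s; the normal approximation reaches it at 5.12 s. An SD near 5 s is therefore what the stated size implies, and 22 is not shown to be wrong.

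**Power of the planned test and of Quade's test.** In Quade's test the times and the covariate are ranked, the time ranks are regressed on the covariate ranks, and the residuals are compared between arms. Simulation with 22 per arm and one covariate gives the following. A standardised effect of 1 means 5 s at SD 5 s; 0.7 means 5 s at SD 5/0.7 = 7.1 s.

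| ρ | Effect 1: planned | Effect 1: Quade | Effect 0.7: planned | Effect 0.7: Quade |
|---|---|---|---|---|
| 0 | about 88% | about 88% | about 60% | 59–60% |
| 0.20 | about 88% | 88–89% | about 60% | about 60% |
| 0.30 | about 88% | about 90% | about 60% | 62–64% |
| 0.45 | about 88% | about 93% | about 60% | 67–68% |
| 0.55 | about 88% | 95–96% | about 60% | 72–74% |

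Ranges show the spread between simulation runs. Type I error was close to 5% for both tests (4.5–5.1% for the planned test, 4.9–5.5% for Quade's). With two uninformative covariates at effect 1, power is 86–87% against about 88% unadjusted.

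**Analytic check with ordinary ANCOVA.** Residual SD = SD × √(1 − R²). The variance is multiplied by 1 + k/(44 − k − 3) for k covariates, with 42 − k degrees of freedom. For SD 5.116 s, R² 0.20 and k = 1:

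- residual SD = 5.116 × √0.80 = 4.58 s; with the inflation √1.025 this is 4.63 s
- noncentrality = 5 / (4.63 × √(2/22)) = 3.58
- power = 0.938, against 0.886 for the unadjusted t-test

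At R² 0, 0.10, 0.20 and 0.30, one covariate gives 0.878, 0.909, 0.938 and 0.962. All four predictors give 0.851, 0.885, 0.918 and 0.948. Four covariates therefore need an R² above about 0.10 just to break even, which is why the number should be kept to one or two.

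**Chance imbalance, in seconds.**

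- *Continuous predictor.* The standardised difference between arms has SE √(2/22) = 0.30. A gap of 0.5 SD or more has probability 0.097 for one predictor, and 1 − (1 − 0.097)⁴ = 0.34 for at least one of four if independent. Such a gap shifts the estimate by 0.5 × √R² × 5.116, that is 0.8 s at R² 0.10 and 1.4 s at R² 0.30.
- *Carriers of one predictor.* If 14 to 18 of the 44 patients are carriers (an assumption), the arms differ by 4 or more in 33–36% of randomisations (hypergeometric). A gap of 4 is 4/22 = 18 points. With carrier proportion p, the shift is (4/22) × ρ × 5 / √(p(1 − p)). This is 0.55–0.59 s at ρ 0.30 and 1.02–1.07 s at ρ 0.55. At ρ = 1 it is still only 1.85–1.95 s.

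**The case against.** The strongest reply is that nothing here is wrong. An unadjusted rank test after 1:1 randomisation is valid, its simulated type I error stays at about 5% even when prognostic covariates exist, and the predictors were recorded for eligibility screening. Recording a variable does not oblige anyone to adjust for it. All of this stands, and it makes the point a matter of efficiency.

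A reader might infer that chance imbalance in airway difficulty could produce or hide the full 5 s. The documents do not support that. For a gap of 4 carriers to move the mean by 5 s, one predictor would have to add 5 / (4/22) = 27.5 s per patient, whereas with SD 5 s even perfect correlation caps the shift below 2 s.

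A reader might also infer that the extra power is free and assured. It is neither. The protocol gives no correlation, and it calls these factors predictors of difficult intubation without saying how strongly they determine time to ventilation. The limit of one predictor narrows their range and may weaken the correlation. Below ρ of about 0.3 the gain is negligible, and with uninformative covariates there is a small loss.

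Finally, an adjusted supportive analysis could sit in a SAP that is not shown. That is fair, but the primary test is named in protocol section 5.2, and a change to it belongs there.

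**Conclusion.** The point holds as a cheap improvement. The plan records baseline predictors and uses them in neither allocation nor the primary analysis, giving up some precision in a 44-patient trial.

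The trade-off favours adjustment: about 2 to 7 points of power gained at a standardised effect of 1, and about 2 to 14 points at 0.7, if the correlation lies between 0.30 and 0.55; about 1 to 2 points lost if the covariates carry no information. The realised estimate would also be protected against chance shifts of roughly 0.6 to 1.4 s.

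These figures rest on normal times, the stated SDs and the assumed correlations, none of which the protocol supplies. The missing SD in section 5.1 is a separate and larger matter. At SD 8 s the unadjusted t-test has power of about 0.53, and one covariate with R² 0.30 raises it only to 0.67, so adjustment is no substitute for a justified sample size.

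**What to change.** In section 5.2, make the primary comparison of time to ventilation a rank ANCOVA (Quade's test) on one, at most two, baseline predictors already on the CRF, for example Mallampati score and mouth opening. Name them before any outcome data are seen. Keep the unadjusted Wilcoxon-Mann-Whitney test as a sensitivity analysis.

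The cost is about one sentence in 5.2 and a two-step calculation, with no new data and no additional patients. The downside is one or two degrees of freedom and the small power loss given above if the chosen predictors prove uninformative.

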**Day of Surgery**

Preoxygenation is achieved using the Standard Operating Procedere of the University Medical Center Mainz. Anesthesia is then induced by injecting anesthetic agents (Opioid, hypnotic-/ and neuromuscular blocking agent). The type and dosage of these drugs are to consider of the intubating physician. Laryngoscopy is performed using the blade allocated at random:

- King Vision standard blade
- King Vision channeled blade

The size of the ETT (7.5 Internal Diameter) is always similar in both groups. The time to ventilation starting by each introduction of the King Vision VL into the oral cavity. The endotracheal tube position is confirmed by analyzing the capnography curve. The overall time to ventilation is defined as the time from inserting the blade into the oral cavity to observation of the first inflection on the expired capnography curve on the anesthesia respirator. The C & L grade of glottis visibility and the POGO scale score are evaluated simultaneously on the monitor display of the King Vision VL. After Intervention the physician asked for his subjective Assessment of the handling with the blade (by means of the Likert scale)

**5. Statistic**

**5.1 Sample Size**

On the basis of previous data (4,7) we expected a difference of five seconds in time to ventilation in the channeled blade group. Assuming that using channeled blade abbreviated the time to ventilation with a Power of 90 %, 22 patients are needed in each group, that is, 44 patients at all.

**5.2 Analysis of the primary outcome**

All data were exported from our CRF into MS Excel (Microsoft, Redmond, WA, USA) for analysis. Statistical testing was performed using Prism 7 (Graph Pad Software, La Jolla, CA, USA). The time to ventilation will be compared between the two groups using the Wicoxon-Mann-Whitney-test. A p-value of <0.05 was considered significant.

**5.3 Analysis of the secondary outcomes**

Secondary outcomes will be using a two-tailed Fischer ’s exact test for categorical data and an unpaired t-test to compare continuous data.

**5.4 Patient analysis**

Only patients in whom the intervention was fully carried out, evaluated in the Statitistical testing. (Per protocol Analysis)

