**8. Administration**

**8.1 Study interventions**

The planning, execution and evaluation of the study is a subject to the require-ments of ICH-GCP and the applicable regulatory requirement.

As protocol violations to understand all deviations from the instructions and procedures described in this study protocol. Examples for this are:

• Lack of data collection or carrying the wrong time

• Lack of Compliance

• violation of inclusion or exclusion criteria

It is the responsibility of the investigator to avoid protocol violations in order to keep the patient after he was included in the study.

It is the duty of all study participants to communicate all protocol violations immediately to the principal investigator and documented. Before statistical analysis which are then discussed with the responsible biostatistician.

It must also be secured by the investigator that all collected from the patient data is documented in the test plan. Minor discrepancies are certainly not to be avoided in everyday work, however, must be documented with justification.

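### Per protocol is the only analysis set, and patients stopped for an unexpected difficult airway are dropped and replaced, so the primary comparison selects on its own outcome after randomisation

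*Protocol*

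**What the plan says.** Section 5.4 settles who is tested: "Only patients in whom the intervention was fully carried out, evaluated in the Statitistical testing. (Per protocol Analysis". No other set is defined. The term "Intention to treat" stands in the abbreviation list, but no analysis section uses it.

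Section 3.5 lists reasons for ending an individual patient's participation. One is "Unexpected emergency or situation under a Difficult Airway" management; another is verbal withdrawal of consent. The same list adds: "Patients who discontinue study participation prematurely replaced". It does not say whether the event must come before randomisation, before laryngoscopy or at any time.

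Section 2.1 defines the primary endpoint as time to first ventilation and adds: "The time limit for the intubation attempt amounts to 120 seconds". It gives no value or rank to an attempt that reaches the limit. Section 4 (Day of Surgery) says: "The time to ventilation starting by each introduction of the King Vision VL into the oral cavity". Section 5.2 names the primary test: "The time to ventilation will be compared between the two groups using the Wicoxon-Mann-Whitney-test".

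The secondary endpoints (protocol overview and section 2.2) are component times, glottic view and the user's rating. None is a success rate, a failure count or a number of attempts.

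**The concern.** Section 3.3 already excludes patients with more than one predictor of a difficult airway. An unexpected difficult airway will therefore mostly be recognised during airway management, when the blade has been allocated and may be in use. Whether the tube can be placed may then depend on the blade, and a patient who cannot be ventilated through it is the worst possible result on the primary endpoint. Removing that patient makes membership of the analysis set depend on the outcome. Filling the group back up to 22 restores the number but not the randomised comparison.

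The trial would then compare times among patients in whom each blade worked. A blade that is quick when it works but fails more often could be declared better with no sign of the failures in any planned test. Section 1.2 gives patient safety as a purpose of the comparison, and these are the patients who bear most on it.

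**Working it through.** **The plan's own figure.** Section 5.1 gives a 5 s difference, 90% power and 22 per group, but no SD, so 22 cannot be reproduced from the stated inputs. Solving the usual formula for the SD at two-sided 0.05:

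SD = 5 / [(1.960 + 1.282) × √(2/22)] = 5.12 s.

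The t-test version gives 5.00 s, and so does multiplying by √0.955 for the efficiency of the Wilcoxon test (5.12 × √0.955 = 5.00). A one-sided test gives 5.67 s by the normal formula. An SD near 5 s is thus what the sample size implies. It is not a figure in the protocol.

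**Inputs to the illustration.**
- From the protocol: 22 per arm, a 5 s difference, the Wilcoxon-Mann-Whitney test, significance level 0.05.
- Assumed: two-sided test; normal times with mean 30 s (standard blade) and 25 s (channeled blade); SD 5 s; failure unrelated to the time the patient would otherwise have had; under the plan as written, replacement continues until 22 patients per arm have completed.

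Each result is the share of simulated trials that are significant in favour of the channeled blade.

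| Failures, channeled / standard | As written | Failures ranked worst |
| --- | --- | --- |
| 0 / 0 | 88% | 88% |
| 1 / 0 | 88% | 79% |
| 2 / 0 | 88% | 64% |
| 3 / 0 | 88% | 43% |
| 4 / 0 | 88% | 21% |
| 5 / 0 | 88% | 7% |
| 1 / 1 | 88% | 83% |
| 2 / 2 | 88% | 76% |

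The as-written column cannot move, because a failed patient never enters the test. One failure is 1/22 = 4.5% of an arm; five are 5/22 = 22.7%.

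**With random failures.** At SD 5.1 s, and failures in the channeled arm only, the as-written figure stays at about 87%. The worst-rank figure is 72%, 55%, 37%, 23% and 6% at failure rates of 5%, 10%, 15%, 20% and 30%.

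**Range for the SD.** The starting level depends strongly on it. For a 5 s difference and 22 per arm, the normal-formula power is 0.99 at SD 4 s, 0.79 at 6 s, 0.55 at 8 s and 0.38 at 10 s. The simulated rank test without failures gives 35% at 10 s. The level changes, but the as-written result ignores failures at every SD.

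**The case against.** The best reply is that failures may be rare. Section 3.3 removes patients with several predictors of difficulty, and section 1.3 says staff are familiar with both devices. With one failure in each arm, the illustration moves only from 88% to 83%. This stands as a limit on size: the larger drops need several failures in one arm and none in the other. It does not rescue the rule, since one or two failures in one arm already give 79% or 64%, and a plan cannot assume there will be none.

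Section 8.1 also requires protocol violations to be documented and discussed with the biostatistician before analysis. That is a safeguard on process. It does not bring stopped patients back into a set that section 5.4 closes to them.

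A reader might infer four stronger points that the protocol does not support:
- *Every attempt beyond 120 s is excluded.* This is the likely reading of section 5.4, but it is an inference. Section 2.1 limits the attempt, and section 4 times each introduction of the device, so a patient intubated on a second introduction may count as completed.
- *Every cancellation is a blade failure.* Consent withdrawn before laryngoscopy is not, and an emergency need not be.
- *Replacement discloses the next allocation.* That would need replacement within the same arm, which section 3.5 does not state. Section 3 describes central 1:1 randomisation.
- *The bias is about 9 s.* Scoring 10% failures at 120 s does shift a mean by 0.10 × (120 − 30) = 9 s, but the primary test uses ranks. With equal times otherwise, the worst-rank test finds the worse blade in only about 8% of such trials.

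**Conclusion.** The concern holds in this form: sections 5.4 and 3.5 together remove and replace patients whose outcome may be the worst result of the allocated blade, and nothing in the endpoint list records them. The difficult-airway rule in section 3.5 is enough to establish this without any assumption about the 120 s limit, whose consequence the protocol leaves unstated. The protocol fixes the analysis set itself, so this is not a detail left to a separate analysis plan.

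The size is conditional. Under the assumed times and SD, about 88% of trials favour the channeled blade as planned, against 79% down to 7% with one to five failures in that arm ranked worst, and 83% or 76% with one or two in each arm. The bias is nil if nobody fails and could favour either blade. Because it bears on the primary comparison, it should be corrected before the analysis.

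**What to change.** Reword sections 5.4 and 3.5:
- Make the primary set all randomised patients in whom laryngoscopy was started, analysed by allocated blade.
- Give the worst tied rank, in the Wilcoxon-Mann-Whitney test already planned, to patients never ventilated through a tube placed with the allocated blade, including those stopped for a difficult airway.
- Allow replacement only where laryngoscopy was never started.
- Report failures by arm, and keep the per-protocol analysis as a sensitivity analysis.

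Reconcile section 2.1 with the Day of Surgery text in section 4, so that it is clear whether the 120 s limit and the clock apply per attempt or per patient, and rank patients who reach the limit accordingly.

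The cost is minor rewording and one success/failure item on the CRF. The result may be less favourable for a blade that fails. The lower chance of a significant result in that case comes from counting the failures and is not in itself a reason to recruit more patients. Clinical handling of the airway is unchanged.

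### Per-protocol testing (5.4) combined with replacement (3.5) lets patients in whom the allocated blade failed be dropped and replaced, and no planned endpoint or analysis compares failures between blades

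*Protocol*

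**What the plan says.** Section 5.4 sets the only analysis population: "Only patients in whom the intervention was fully carried out, evaluated in the Statitistical testing". It labels this per protocol. No other population is specified; ITT appears only in the abbreviation list.

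Section 3.5 (3.4 in the index) lists what ends an individual's participation. Besides withdrawal of consent, the trigger is "Unexpected emergency or situation under a Difficult Airway" management. The same list adds "Patients who discontinue study participation prematurely replaced".

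Section 2.1 makes time to first ventilation the primary endpoint and adds "The time limit for the intubation attempt amounts to 120 seconds". It gives no rule for a patient who reaches that limit, and 3.5 does not list the limit as a stopping reason. Section 4 fixes the clock: "The overall time to ventilation is defined as the time from inserting the blade into the oral cavity" until the first capnography deflection. It also speaks of each introduction of the device, so more than one insertion seems to be foreseen.

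For the test, section 5.2 states "The time to ventilation will be compared between the two groups using the Wicoxon-Mann-Whitney-test". The secondary endpoints in 2.2 are component times, glottic view and a Likert rating. For these, 5.3 names Fisher's "exact test for categorical data and an unpaired t-test to compare continuous data".

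**The concern.** A time to ventilation with the allocated blade exists only if that blade achieves intubation. A difficult-airway situation arises after randomisation and can be caused by the blade. If such patients leave the analysis and are replaced by patients who were intubated, each arm is filled with successes and the groups tested are no longer the groups randomised.

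Two things can then go wrong. First, a blade that is quick when it works but fails more often is judged only on the occasions when it worked. Second, if failures cluster in airways that would have taken longest, the arm with more failures loses its hardest patients, and even the comparison among successes is no longer like with like. Both favour the blade that fails more often.

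Section 1.2 says the comparison is meant to serve patient safety and to inform purchasing by other hospitals. For both purposes, failure of the device matters at least as much as a few seconds. This is also not a detail left open for a statistical analysis plan. The protocol fixes the analysis set and the replacement rule, and a later plan that kept failures would contradict 5.4.

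**Working it through.** **1. Three patients traced through the text.**

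| Patient, after blade insertion | 3.5 | 5.4 | Outcome |
| --- | --- | --- | --- |
| Difficult-airway situation | Participation ends, replaced | Not completed | Exclusion directed |
| Reaches 120 s, then intubated with the allocated blade on a later insertion | Not listed | Completion undefined | May be kept or dropped |
| Reaches 120 s, then changed to another device | Not listed as such | Hard to read as completed | Exclusion likely, replacement possible |

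None of these events is an endpoint in the overview, 2.1 or 2.2.

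**2. The plan's sample size.** Section 5.1 gives 5 s, 90% power and 22 per group, but no SD, so 22 cannot be reproduced directly. Back-solving at a two-sided 5% level (an assumption):
- Normal approximation: SD = 5 × √(22/2) / (1.960 + 1.282) = 5 × 3.317 / 3.242 = 5.1 s.
- Exact t-test: standardised difference 1.0005, so SD = 5 / 1.0005 = 5.0 s.

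**3. How few failures matter.** One failure is 1/22 = 4.5% of an arm. The chance of at least one in an arm is 1 − (1 − p)^22. This is 36% at p = 2%, 68% at 5% and 90% at 10%. All these rates are assumptions.

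**4. The two analyses compared.** Simulation with 22 per arm, normal times, SD 5.0 s and one blade truly 5 s faster when it works. Failures are random with respect to time. The test is the two-sided Wilcoxon-Mann-Whitney test, corrected for ties and continuity. The entries are the share of trials that call that blade faster.

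| Failures | Dropped and replaced | Kept, ranked last |
| --- | --- | --- |
| None | 88% | 88% |
| Faster arm only, 2% | 88% | about 84% |
| Faster arm only, 4.5% | 88% | 76% |
| Faster arm only, 9% | 88% | 60% |
| Faster arm only, 14% | 88% | 43% |
| Both arms, 4.5% each | 88% | 80% |
| Both arms, 9% each | 88% | 71% |
| Exactly 1 of 22, slower arm only | 88% | 91% |

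The levels depend on the SD. At 7 s the no-failure figure is about 61%, and it falls to about 46 to 47% with 4.5% failures in the faster arm. At 10 s the figures are about 35 to 36% and 23%.

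With no time difference among successes and 15% failures in one arm (SD 5.1 s), the drop-and-replace test finds the failing blade worse in 2.5% of trials, which is chance. Ranking failures last finds it in 13.6%.

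**5. What a success comparison could show.** Fisher's exact test, two-sided, 22 per arm: 0 v 3 gives p = 0.23, 0 v 4 gives 0.11 and 0 v 5 gives 0.048. For 3/22 − 0/22 = 13.6 points, the Newcombe 95% interval is −3.7 to 33.3 points.

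**The case against.** The strongest reply is that step 4 measures no bias. With failures random with respect to time, the comparison among successes is unbiased for the question it answers, and calling the blade faster in 88% of trials is right. The fall towards 43% comes from asking a different question, time and failure together, at one back-solved SD. This stands. A reader might take the gap between the columns as the size of the error; the documents give neither an SD nor a failure rate and cannot support that.

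A reader might also infer that every patient who reaches 120 s is excluded. The text does not say so: the limit is not a stopping reason in 3.5, and a patient intubated on a later insertion can be read as having completed the intervention. The difficult-airway stop is a safety rule and need not be the blade's doing.

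Nor is it right that the loss would go unseen. Section 7.2.1 asks for missing data to be explained, and 8.1 requires deviations to be documented and discussed with the biostatistician before analysis. What remains is that documentation is not a comparison: no endpoint or analysis sets failures in one arm against the other.

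Finally, failures may be rare. Patients are elective, those with more than one difficult-airway predictor are excluded (3.3), and staff know both devices (1.3). This is fair, and it makes the harm conditional. It does not remove the rule that causes it.

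**Conclusion.** The point holds in a limited form. Sections 5.4 and 3.5 together allow blade-related failures after randomisation to be dropped and replaced, so the primary comparison can be conditioned on success and can favour the blade that fails more often. For difficult-airway withdrawals this is directed; for the 120 s limit it is only possible. No planned endpoint or analysis compares failures.

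The size of any bias is unknown. With no failures it is zero from this source. The percentages in the working rest on an assumed SD and assumed failure rates, and they show only how far two analyses of the same trial can differ. The primary clock is not at issue: the overview's "Comparison of the overall intubation time between the Channeled and the Standard Blade" and the definition in section 4 largely settle it. The change should be made because it is cheap and the arms are small, not because a distorted result has been shown.

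**What to change.** - **3.5:** limit replacement to patients in whom the allocated blade was never inserted.
- **5.4:** make the main analysis all randomised patients in whom the blade was inserted, by allocated blade. Keep per protocol as supportive.
- **Primary comparison:** a patient finally ventilated through a tube placed with the allocated blade keeps the observed overall time of section 4, also after more than one insertion. A patient never intubated with that blade (device change, or withdrawal for airway difficulty after insertion) is tied at the longest rank in the planned Wilcoxon-Mann-Whitney test.
- **2.1:** leave the 120 s limit per attempt as it is. Counting 120 s from the first insertion as failure would change the limit and would tie patients who have an observed time with patients never intubated.
- **2.2:** add success with the allocated blade at the first attempt within 120 s (yes/no) and number of insertions. Report both by arm, success with a confidence interval and the Fisher test of 5.3. Read the success comparison as descriptive, since 0 v 5 of 22 is needed for p < 0.05.

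The cost is a few CRF fields and short edits; both tests are already named. The primary result then reflects time and failure together. Power falls if both arms have failures: at an assumed SD of 5 s, from 88% to about 80% at 4.5% each and 71% at 9% each, and it is lower throughout at a larger SD. If no failures occur, nothing is lost.
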